10.3 Adequacy of Protection Against Risks

10.3.1 Recruitment and Informed Consent

- Recruitment will only begin once the Indiana University Institutional Review Board has approved this study and advertisements to the community for the HIV-uninfected control participants. All subjects will be recruited from the outpatient HIV care clinics at Indiana University and Wishard Memorial Hospital. Self-referrals from other venues will also be considered. If the primary caregiver for the patient believes he or she is eligible for the study and allows the patient to be approached for screening, one of the study investigators or a study nurse will approach each potential participant during his or her regularly scheduled clinic visit. If eligibility is confirmed, then the purpose, procedures, and risks and benefits of the study will be discussed with the subject. Subjects will have ample opportunity to ask questions and to have all concerns addressed. If the subject wishes to pursue screening, then written informed consent will be obtained (and a copy given to the subject). All consent forms will be stored in a locked file cabinet.

10.3.2 Protection Against Risk

10.3.2.1 Confidentiality. To minimize the risk to subject confidentiality, patient identifiers will be removed once his or her data is abstracted and recorded, and only the random study identification number (generated when consent is provided) will be used. All hardcopy study data will be kept in a secured and locked file cabinet. All electronic data will be kept in a password-protected computer database. The only link between patient identifiers and the randomized study identification number will be kept in separate files. Identifiers will never be used in the analysis or presentation of study results.

10.3.2.2 Blood draws. The risks of blood drawing will be minimized by having only experienced medical personnel perform this procedure. The amount of blood that will be drawn falls well within safety standards for blood donation.

10.3.2.3 Pentoxifylline. Our pilot data and safety results from the literature suggest that PTX is very well-tolerated, so we do not expect any serious adverse events from use of this agent. However, to minimize potential risks with this drug, the eligibility criteria will reduce the potential adverse events associated with this drug by excluding those at higher risk. Adverse events will be monitored for closely. Safety laboratories (complete blood cell counts including platelet counts, chemistries, renal and liver function tests) will be obtained at each main study visit or upon development of symptoms. Grade III or IV abnormalities (defined using the Division of AIDS Table for Grading Adult Adverse Experiences) will prompt immediate discontinuation of the drug. Pregnant and breastfeeding women will be excluded. Women of reproductive age will be asked to use two forms of contraception during the clinical trials.

10.3.2.4 Nitroglycerin. Brachial artery reactivity testing will be performed in a controlled setting in the Indiana Clinical Research Center. To protect against the risks of nitroglycerin administration, registered nurses in the ICRC will monitor the subject’s blood pressure throughout brachial reactivity testing. Subjects with inherent resting hypotension will be excluded from the NTG-mediated flow dilation portion of the brachial reactivity testing. If the subject becomes symptomatic (e.g. dizzy, perspiring, weak or nauseated, or if the systolic blood pressure falls below 80mmHg or more then 30mmHg below their baseline systolic blood pressure, the study will be stopped immediately). The patient will be placed in Trendelenberg position and be given fluids through the previously placed IV heplock if the blood pressure does not recover spontaneously. If the patient develops a headache, an analgesic will be recommended.

10.3.2.5 Withholding Antiretroviral Therapies. Subjects will be included if their HIV caregiver has decided that antiretroviral therapy is not required and thus has been free of cART for at least six months time. There is a minimal risk to the subjects by continuing to refrain from use of antiretrovirals during the short course of this trial (maximum 11 weeks from screening to last main visit). To reduce this small risk, subjects must have CD4 cell counts above 350/µL, which is the level that the Department of Health and Human Services HIV Management Guidelines (<http://aidsinfo.nih.gov/contentfiles/AdultandAdolescentGL.pdf>) states that initiation of ART is not required. Per these guidelines, CD4 cell counts need only be routinely monitored every 3-4 months (12-16 weeks) in the untreated, asymptomatic patient. Therefore, the study course for each subject should be completed by the time their CD4 cell count would normally be rechecked in the clinic. However, if the subject develops signs, symptoms, or conditions associated with a reduction in CD4 cell count, the subject will have their CD4 cell count checked immediately. The principal investigator and the primary caregiver will then decide if antiretroviral therapies should be started immediately with permanent discontinuation of this study.

- - - 1. Adverse Event Management and Reporting. In the event of an adverse event, necessary medical and professional intervention will be provided immediately and billed to the subject’s medical insurance (if available). If the subject does not have insurance, care will be provided via the indigent care program at Wishard Memorial hospital. Standard procedures for reporting deviations from protocols and serious adverse events will be reported to the Indiana University IRB within 30 days (standard protocol). Deaths will be reported within 3 days. All adverse events will be graded using The Division of AIDS Table for Grading Adult Adverse Experiences is located at: <http://roc.s-3.com/members/download/adulttox.pdf>.
      2. Data and Safety Monitoring Committee. [name] (Indiana University Division of Nephrology) will serve as the Chair of the independent Data and Safety Monitoring Board for investigations proposed here. Drs. [name] and [name] (as co-PIs on this application) and [name] (as protocol statistician) will also be members of this board.
  1. Potential Benefits of the Proposed Research to the Subjects and Others

Potential benefits include an evaluation of their cardiovascular and immunologic status. They may also derive short-term benefits from the provision of pentoxifylline, although this is not guaranteed. Additionally, the nominal reimbursement for the subject’s time and effort may provide valuable resources for both the subject and his/her dependents. Finally, the subjects may also benefit from knowing that their participation will accrue knowledge that could benefit other HIV-infected patients.

Although there are no guaranteed clinical benefits from those who are randomized to treatment with pentoxifylline, this agent appears quite safe when used in HIV-infected subjects. The standard of care will not be altered in the control subjects. Therefore, the ancillary benefits to the participants in the proposed studies significantly outweigh the minimal risks in this study. Moreover, the proposed research may lead to other prevention and therapeutic studies that would demonstrate how to improve endothelial function and reduce future cardiovascular events in the HIV-infected population. This would benefit society directly by impacting clinical practice.

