3.3 Main study visits

After the subject has entered the study, s/he will come to the Indiana Clinical Research Center for the initial Week 0 (Entry) visit within three weeks of the screening visit. The subject’s medical records will be re-examined for clinical variables of interest. Adherence to study drug will be assessed by pill count, three-day recall, and eventually by PTX level which will be measured in batch at the end of each trial. To assess the success of the blinding mechanism/allocation, both the subjects and study nurse will be asked if they thought the subject was randomized to either PTX or placebo at study closeout.

Vital signs and anthropometrics will be measured per AIDS Adult Clinical Trials Group recommendations (<http://aactg.s-3.com/members/download/other/metabolic/>). The subject will provide fasting, morning blood samples for markers of cardiovascular risk, inflammation, endothelial activation, immune activation, and metabolism. All specimens not required for real-time safety monitoring will be frozen and batch-tested at the end of these studies to reduce interassay variability. The lone exception will be the flow cytometry measurements for activated CD8 cells, which will necessarily be performed on fresh whole blood samples.

The subject will then undergo brachial artery reactivity testing as outlined by the International Brachial Artery Reactivity Task Force [130]. The procedure for measuring brachial reactivity will require one hour of the subject’s time. There will be no documentation on the ultrasound scans regarding the HIV status (HIV-positive for the trial participants vs. HIV-negative for the external control subjects) or the randomization assignment of the participants in the two trials. This will ensure that [name], who will assess all the ultrasound results, will be blinded to these two key variables. All members of the study team will be blinded to the drug assignment for those subjects in the clinical trials. Female participants of reproductive potential will have their main study visits during the same phase of their menstrual cycle to minimize confounding by hormonal changes that may affect FMD results [131, 132]).

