1. ADVERSE EVENT MANAGEMENT

The management guidelines listed here are for the adverse events most likely to occur during this protocol. Grade III or IV abnormalities (defined using the Division of AIDS Table for Grading Adult Adverse Experiences) will prompt immediate discontinuation of the drug. For all toxicities that requires pentoxifylline to be permanently discontinued, relevant clinical and laboratory tests will be repeated as needed until there is final resolution or stabilization of the toxicity. Clinical management decisions will be made by the principal investigator in conjunction with the subject’s primary caregiver; care plans and outcomes must be included in the source documentation. Serious adverse events (SAEs) will be documented on CRFs and forwarded to the Indiana University IRB within 10 working days of the event.

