9.3.4 Randomization

26 HIV-infected patients not on cART will randomly be assigned to either the placebo or the pentoxifylline groups. The study statistician will generate a computerized randomization plan that will employ a certain block size for this trial. The block size will be known only to the statistician to maximize blinding for the subject and other study investigators.

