10.2.3 Potential Risks

- There are minimal risks to the subjects enrolled in the proposed research. The first is the potential loss of subject confidentiality. The second consists of the risks associated with blood drawing/needle sticks, which include pain, bruising, infection, and phlebitis. The amounts of blood to be drawn at screening and at each main study visit are 15cc (one tablespoon) and 45cc (three tablespoons), respectively. The total amount of blood to be obtained would be approximately 150cc (10 tablespoons) over at least 11 weeks. The primary risks associated with the use of pentoxifylline are gastrointestinal (nausea, vomiting, dyspepsia), flushing, and dizziness. PTX is a Pregnancy Category C drug and is found in breastmilk. There are no known or potential interactions with antiretroviral medications or commonly used therapies in the HIV-infected population. Nevertheless, we will carefully monitor CD4 counts and HIV-1 viral loads to assess for any potential worsening of immunologic/virologic status for those randomized to PTX during these studies and will be evaluated carefully by the DSMB. The primary risks associated with nitroglycerin administration as part of the brachial artery testing are headache and transient hypotension. NTG may also infrequently cause the sensation of flushing of the skin and rash. There may also be moderate pain associated with the inflation of forearm cuff as part of the brachial reactivity testing.
- The principal alternative to these procedures would be not to participate in the research.

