10.6 Data and Safety Monitoring Plan

Progress of these studies, including data monitoring, subject enrollment, protocol deviations, and all SAE, will be reviewed by a panel including the PIs (Drs. [name] and [name]), the study statistician ([name]), and an expert investigator at Indiana University not directly connected with this study ([name]; Division of Nephrology, Indiana University). Reports, which will include descriptions of all adverse events, will be prepared for review by this panel every 6 months. Any study prematurely terminated due to an adverse event will be reviewed immediately. Standard procedures for reporting deviations from protocols to the I CRC, IRB, and NHLBI will be implemented. Serious Adverse Events (SAEs) will also be reported to the IRB within 3 working days and subsequently forwarded to NHLBI as required.

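### The board called independent is three-quarters study team, its review of PTX subjects cannot be squared with the stated full-team blind, and three sections give different SAE deadlines to the IRB

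*Combined protocol and SAP*

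**What the plan says.** **Board.** Under section 10.3.2.7, an investigator from the Division of Nephrology "will serve as the Chair of the independent Data and Safety Monitoring Board for investigations proposed here". The same paragraph adds the two co-PIs and the statistician: "as protocol statistician) will also be members of this board". Section 10.6 describes a review panel with the same four roles and identifies only the nephrology investigator as not directly connected with the study. Panel reports are due every six months and describe all adverse events.

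**Task.** Section 10.2.3 says CD4 counts and viral loads will be watched for worsening in "those randomized to PTX during these studies and will be evaluated carefully by the DSMB".

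**Blind.** Section 3.3 states: "All members of the study team will be blinded to the drug assignment for those subjects in the clinical trials". It makes no exception. Under section 9.3.4, "The study statistician will generate a computerized randomization plan", and the block size is known to that person alone.

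**SAE reporting to the IRB.** The introduction to section 7 has SAEs "forwarded to the Indiana University IRB within 10 working days of the event". Section 10.3.2.6 says "serious adverse events will be reported to the Indiana University IRB within 30 days (standard protocol"). Section 10.6 says "Serious Adverse Events (SAEs) will also be reported to the IRB within 3 working days". Section 10.3.2.6 also sets a separate limit of 3 days for deaths.

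**The concern.** The protocol makes two assurances, an independent board and a fully blinded study team, that its own membership list and role assignments contradict.

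This matters most for the co-PIs. Sections 7.2 to 7.3.4 let the primary investigator (or the primary caregiver) keep a subject on drug when there is compelling evidence that an event is not due to PTX. Section 8 lets the investigators withdraw subjects judged at risk of non-compliance. Knowledge of results by arm could colour those decisions, and they affect who reaches the week 8 scan. Section 9.2 plans for 10 evaluable subjects per group out of 13 recruited, a margin of 13 − 10 = 3 per arm.

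The reporting deadlines are a separate matter. Staff can comply with one section and still be late under another.

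**Working it through.** No power or alpha figure is at issue, so there is no stated figure to reproduce. The check is a comparison of sections plus three small counts.

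1. **Membership (10.3.2.7, 10.6).** Chair 1 + co-PIs 2 + statistician 1 = 4 members. Study team: 2 + 1 = 3, so 3/4 = 75%.

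2. **Task against blind.** Set three statements side by side:
   - (a) The board evaluates worsening in those randomized to PTX (10.2.3).
   - (b) The co-PIs sit on the board (10.3.2.7).
   - (c) Every member of the study team is blinded (3.3).

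   Singling out the PTX group needs either the assignments or a summary split by arm. With (b), that material reaches the co-PIs unless something separates them from it. Sections 3.3, 9.3.4, 10.2.3, 10.3.2.7 and 10.6 describe no closed report, masked label or recusal. If the board saw pooled data only, (c) would hold but (a) would not be carried out. The three statements cannot all be followed as written.

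3. **Statistician.** Whoever generates the randomization plan (9.3.4) can know the assignments, so (c) is inaccurate for that role. Section 9.3.2 also leaves data-dependent steps open: covariates are kept or dropped by significance, and transformations depend on how the data look. The documents do not say who takes these steps and name no second statistician.

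4. **Number and size of reviews (9.5, 10.6).** Expected duration is 16 months: 16/6 = 2.7, so 2 six-monthly reviews. With the 6-month contingency it is 22 months: 22/6 = 3.7, so 3 reviews. At 2 enrolments per month:
   - Month 6: 2 × 6 = 12 subjects, about 6 per arm.
   - Month 12: 2 × 12 = 24 subjects, about 12 per arm.
   - Month 18: all 26 subjects, 13 per arm.

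5. **SAE deadlines.** These use a five-day working week and read the 30 days as calendar days.
   - Section 10.6: 3 working days, which is 3 to 5 calendar days.
   - Section 7: 10 working days, about 10/5 × 7 = 14 calendar days.
   - Section 10.3.2.6: 30 days.

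   Ratio of longest to shortest: 30/5 = 6 to 30/3 = 10. A report sent on day 30 meets 10.3.2.6 but is 30 − 5 = 25 to 30 − 3 = 27 days past the limit in 10.6. The limit for deaths covers only a subset of SAEs and does not settle the rest.

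**The case against.** The strongest reply is that nothing says the board sees data by arm. Section 10.6 lists what the panel reviews (data monitoring, enrolment, deviations, SAEs and adverse event descriptions) and mentions no table by treatment. Section 10.2.3 is a loosely worded risk statement, not a report specification. This stands as a limit on the claim. A reader might infer that the co-PIs will be unblinded; the documents support only that the task implies it and that no safeguard is described.

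A reader might also infer that by-arm reports in so small a trial would reveal individual assignments. No listing is described. Arm-level summaries need not identify anyone; subject-level listings with the arm shown would.

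Nor can it be said that the trial lacks a blind. Drug is over-encapsulated with matching placebo (5.2), scans carry no assignment and the reader is blinded (3.3), the block size is withheld (9.3.4), blinding is assessed at closeout (6.3.8.10), and analysis is by intention to treat (9.1). These protect the FMD measurement itself. What remains is the indirect route through relatedness, dosing and withdrawal decisions.

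On the statistician, section 9.3.4 already sets that role apart from the other investigators, and section 9.3.2 names the candidate covariates and gives a rule for dropping them. The fault there is mainly the blanket wording in section 3.3.

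On SAEs, deaths have a short limit, and section 3.3 requires immediate assessment of events possibly related to drug. Both reduce the likely harm but leave the contradiction in place. Finally, a small trial of a marketed drug may not need a fully external board. That is fair, but this protocol claims independence, so it should either provide it or change the claim.

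**Conclusion.** The point holds as a contradiction in the text with a plausible but indirect route to bias. Three of four board members are study team. The evaluation of PTX subjects is incompatible, as written, with the stated blind for the co-PIs, and the blind is misstated for the statistician. About 2 to 3 six-monthly reviews would be affected. The SAE deadlines conflict outright, by roughly 6- to 10-fold, and that part needs no inference.

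The conclusion assumes that the board in 10.3.2.7 and the panel in 10.6 are the same body, that the protocol statistician and the study statistician are the same person, and that the primary investigator in section 7 is one of the co-PIs on the board. The matching role descriptions support the first two. This should be corrected, but it does not invalidate the design.

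**What to change.** - **10.3.2.7 and 10.6:** state that any report by treatment arm goes only to the unconnected chair and that the co-PIs see pooled data only. Align 10.2.3 with this.
- **Independence:** either drop that description of the board or make the study-team members non-voting.
- **3.3:** state that the statistician who holds the list is an exception to the blind.
- **9.3.2:** fix the covariate and transformation choices on data without arm labels. The covariate step as written keeps the intervention term in the model, so that step would have to be reworded.
- **7, 10.3.2.6 and 10.6:** reconcile to a single SAE deadline. This review does not say which is right.

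The cost is protocol wording. The co-PIs give up arm-level data during the trial, and the chair becomes the sole reader of by-arm reports. The protocol should therefore say who prepares them; the documents name nobody for this, and the list-holding statistician is one option.

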10.5 Importance of the Knowledge to be Gained

The knowledge that will be gained from this study will determine the relationships between HIV, inflammation, and endothelial dysfunction. This would potentially impact the clinical care of HIV-infected patients at risk for cardiovascular disease. Furthermore, prevention and therapeutic strategies (including the use of the inexpensive agent pentoxifylline) for these highly prevalent diseases can then be formulated, thereby reducing morbidity, mortality, and cost to the patients and society in general.

Again, the risks to the subjects are considered minimal. Even if the results are negative, the results of these investigations will add substantially to our knowledge on the mechanisms underlying endothelial dysfunction in HIV-infected patients. Therefore, the importance of the knowledge gained outweighs the risks to the participants.

10.6 Data and Safety Monitoring Plan

Progress of these studies, including data monitoring, subject enrollment, protocol deviations, and all SAE, will be reviewed by a panel including the PIs (Drs. [name] and [name]), the study statistician ([name]), and an expert investigator at Indiana University not directly connected with this study ([name]; Division of Nephrology, Indiana University). Reports, which will include descriptions of all adverse events, will be prepared for review by this panel every 6 months. Any study prematurely terminated due to an adverse event will be reviewed immediately. Standard procedures for reporting deviations from protocols to the I CRC, IRB, and NHLBI will be implemented. Serious Adverse Events (SAEs) will also be reported to the IRB within 3 working days and subsequently forwarded to NHLBI as required.

10.7 Inclusion of Women and Minorities

There are no exclusion criteria based on gender, racial category, or ethnicity in the proposed studies. Please see the attached Targeted/Planned Enrollment Table. Based on our previous cumulative experience and the general HIV-infected population cared for at the study sites at Indiana University, it is anticipated that approximately 25% of the study subjects will be women. Pregnant women will be excluded due to the confounding effects of pregnancy on cardiovascular physiology and because pentoxifylline is a Pregnancy Category C agent; we will ask all women of reproductive potential to use two forms of contraception during study participation. Breastfeeding women will also be excluded due to the presence of PTX in the breastmilk of women using pentoxifylline.

It is anticipated that approximately 40% and 8% of the study subjects will be black and Hispanic, respectively. American Indians, Alaskan Natives, Asians, Native Hawaiians or Other Pacific Islanders are not expected to be represented in the proposed study population due to extremely low representation of these groups within the Indiana University Medical Center outpatient clinics and in Indianapolis in general.

